## Abstract

**Background:**

Public health authorities have recognized lack of hand hygiene in hospitals as one of the important causes of preventable mortality and morbidity at population level. The implementation strategy *ACCOMPLISH *(Actively Creating COMPLIance Saving Health) targets both individual and environmental determinants of hand hygiene. This study aims to evaluate the cost-effectiveness of a multicomponent implementation strategy aimed at the reduction of healthcare associated infections in Dutch hospital care, by promotion of hand hygiene.

**Methods/design:**

The *ACCOMPLISH *package will be evaluated in a two-arm cluster randomised trial in 16 hospitals in the Netherlands, in one intensive care unit and one surgical ward per hospital.

**Discussion:**

This study is the first RCT to investigate the effects of a hand hygiene intervention programme on the number of healthcare associated infections, and the first to investigate the cost-effectiveness of such an intervention. In addition, if the ACCOMPLISH package proves successful in improving hand hygiene compliance and lowering the prevalence of healthcare associated infections, the package could be disseminated at (inter)national level.

**Trial registration:**

NTR2448

## Background

Public health authorities have recognized lack of hand hygiene (HH) as one of the important causes of preventable mortality and morbidity at population level [1-3]. Both at national (i.e. UK, USA, The Netherlands) and international levels (World Health Organisation) poor HH has been identified as a threat to public health. HH compliance rates are universally low, leading to unacceptably high rates of healthcare associated infections (HAI), and resulting in unnecessary excess mortality and morbidity in the population and increased healthcare costs due to increased length of hospital stay and more complex care [4].

Guidelines stipulating when HH is required have been in place for many years, but are often not adhered to. Two thirds of the studies included in a systematic review reported compliance rates below 50% [5]. To address the problem of low compliance, many interventions have been designed and evaluated, but the effects are often short lasting or moderate [6]. Grol and Grimshaw made an inventory of the most common interventions used to improve HH practices and described that educational interventions have only short term effects, reminders have a sustained but only modest effect, and performance feedback may be effective, but only if feedback is continued [7]. They concluded that a comprehensive plan, targeting different problems and barriers to change with strategies at different levels (professional, team, patient, and organisation) is needed to achieve lasting changes in HH routines.

It is increasingly recognized that the observed failure to achieve large and sustained effects is due to the absence of well-designed implementation strategies using insights from the behavioural sciences [8,9]. Such strategies are based on a good understanding of factors that contribute to compliance at both the individual and environmental level. Therefore we previously conducted a study that investigated the behavioural correlates of hand hygiene behaviour. This study revealed that the hand hygiene behaviour of physicians and nurses is influenced by different factors (unpublished data [name] et al). Contrary to previous interventions, this knowledge should be used in the design of new strategies to improve compliance. But in accordance with the conclusions of Grol and Grimshaw, the study also revealed that factors at other levels than the individual healthcare worker (HCW), including specific barriers for change, should be targeted as well. Even though HCW know they should perform HH in order to protect both themselves and their patients, negative role models, poor accessibility of materials and a poor social culture can hamper good HH [10]. This so-called intention-behaviour gap has been targeted successfully in other fields by using implementation intentions and recently this method has also been applied to hand hygiene improvement [11,12].

The knowledge gained from our previous behavioural research has therefore been used to develop ACCOMPLISH (Actively Creating COMPLIance Saving Health): a multicomponent implementation strategy to improve the hand hygiene behaviour of physicians and nurses. ACCOMPLISH has the potential to substantially increase compliance and reduce HAI in Dutch hospitals, but experimental implementation and evaluation of this package is necessary before large-scale dissemination in healthcare practice can be advised.

## Objectives

This study aims to evaluate the cost-effectiveness of the *ACCOMPLISH *package and will test the effects of this implementation strategy on HH compliance and prevalence of HAI. Furthermore, an economic evaluation will investigate the cost-effectiveness of this strategy from a healthcare perspective.

Research questions:

1. What is the effect of the multicomponent implementation strategy *ACCOMPLISH *on HH compliance rates?

2. Which process indicators contribute most substantially to observed changes in HH compliance?

3. What is the effect of the multicomponent implementation strategy *ACCOMPLISH *on the prevalence of HAI?

4. What is the balance between costs and health effects (costs per prevented HAI) of the *ACCOMPLISH *package?

## Methods/Design

### Study design

The ACCOMPLISH package will be tested in a two-arm cluster randomized trial in 16 hospitals in the Netherlands (eight intervention and eight control) in one intensive care unit (ICU) and one surgical ward per hospital. In eight hospitals *ACCOMPLISH *will be introduced, while eight control hospitals will maintain normal HH practices. All infection prevention activities as well as any large outbreaks or other major events which might influence HH behaviour will be documented in a process evaluation. The primary outcome measure will be the observed hand hygiene compliance rate, measured at baseline (T1) and after 6 (T2), 12 (T3) and 18 (T4) months. As a secondary outcome measure the prevalence of HAI will be measured at the same time points. At each time point data identifying process indicators will be collected. The process evaluation will also include determinants of implementation, namely the social-political context, the organization, the adopting person (i.e. the HCW), the innovation itself and the facilities needed for implementation [13]. See figure 1 for an overview of the data collection activities.

**Figure 1 F1:**
[figure not shown]
**Study design ACCOMPLISH trial**.

### Area of study

A multicenter study of 16 hospitals in the Netherlands.

### Sample for study

The sample of 16 hospitals will include university teaching hospitals, large general hospitals, small general hospitals and non-academic teaching hospitals and will de randomised at hospital level. Target population: nurses and physicians with direct patient contact working in the ICU or surgical ward at the participating hospitals in the Netherlands.

## The Intervention

### Intervention program: theoretical background

ACCOMPLISH is evidence and theory based, by following a planned stepwise behavioural research approach to intervention development [14]. It focuses on individual level factors, increasing personal and normative feedback, and is embedded in self-regulation theory, which suggests that behaviour-change is a dynamic process, in which specific, achievable goals need to be set, discrepancies between desired goals and goal progress need to be fed back to an individual, and finally (social) reinforcement is an important element to promote behavioural sustainability and ongoing goal pursuit [11,15]. Among others, it addresses these elements by means of increasing planning, performance feedback, increasing knowledge of HH guidelines on an individual level and on environmental factors creating an increased availability of alcohol based hand rub and increasing the visibility of HH guideline support. These factors were identified as major determinants of non-compliance in a previous study (unpublished data, [name] et al.).

The ACCOMPLISH package includes changes to the physical and social environment, performance feedback & goal setting, training and action planning (see table 1):

**Table 1 T1:** Content of the intervention, including operationalisation and targeted behavioural correlate

Content of intervention	Operationalised as	Target behavioural correlate
Physical environment	Electronic alcohol based hand rub dispenser	Habit, availability of materials

	Posters and reminders in workplace	Raise awareness

Social environment	Interactive team training sessions	Social and descriptive norms, goal setting, role models

Education	E-learning modules	Factual knowledge, risk perception, action plans, planning

Performance feedback	Feedback of frequency data: monthly reports with reward	Social norms, self-regulation

1. The physical environment will be adapted by improving the availability of alcohol based hand rub by electronic dispensers with an electronic feedback system. These dispensers will enable easy access and also remind HCW to perform HH at the point of care. The dispensers register each use with a time stamp, which will be used for periodic feedback.

2. The social environment will be targeted with training at group and individual level based on the Helping Hands team training package, to improve social and descriptive norms. [Huis *et al. Helping Hands: a cluster randomised trial to evaluate the effectiveness of two different strategies for promoting hand hygiene in hospital nurses, submitted*] The unique contribution of this part of the intervention is built upon the Social Learning Theory,[16] the Social Influence Theory,[17] the Theory on Team Effectiveness,[18] and the Leadership Theory [19]. The key elements of the training are: gaining active commitment and initiative of ward management and team members, modelling by informal leaders at the ward, setting norms and targets within the team, identifying barriers and formulating activities to improve. This team training will be delivered to nurses and physicians separately. The physician teams will receive one interactive group session, and a web-based session for individual completion a month later. The nurse teams will receive three interactive team sessions during a period of 3-4 months. The interactive sessions will be led by a specially trained coach. During the intervention period the ward manager actively supports the team.

3. Performance feedback is an effective tool to increase awareness, and has often been effective in improving HH for short periods [20]. Through periodical performance feedback of HH frequencies, as measured by the novel dispenser mentioned above, a sustained positive effect on hand hygiene behaviour could be accomplished. Different mediums will be used for communicating the feedback (i.e. newsletters, electronic feedback) and will be imbedded into pre-existing work routines. A reward programme will be linked to the performance feedback in order to provide positive reinforcement of the desired behaviour (i.e. ward with highest increase in compliance).

4. An e-learning module will be used for education purposes, focussing on increasing factual knowledge, risk perception and the formulation of action plans. The module will be used for both physicians and nurses, but tailored to their specific behavioural correlates. Planning will be increased by making action plans (implementation intentions), as part of the training in which HCW will be assisted in making concrete plans and formulating solutions to the everyday problems they encounter concerning HH, using if-then plans. Concretely, it will involve formulating plans how and when they intend to perform hand hygiene (i.e. if I am about to examine a patient in the ICU, then I first walk past the alcohol based hand rub dispenser), as has been successfully used in other areas of public health [21] and more specifically for improving hand hygiene [12].

### Implementation

In order to increase the chances of successful implementation, an extensive communication strategy will be put in place prior to the start of the intervention period.

In each hospital contact persons will be appointed: the Infection Control Practioner (ICP), who will act as a coordinator for all activities, and also as the primary contact between the researchers and hospital. Other contacts will include medical staff, nurses and managers form each hospital, to stimulate active participation in the study by all groups.

At the start of the intervention a festive kick-off meeting will be planned in the participating units, in which HCW will be informed about the intervention activities. Special attention will be paid to the reasons for a process evaluation during the study. HCW will be instructed as to how they can signal when a component of the intervention is interfering with their work activities, so that effective measures to solve these problems can be set in motion swiftly. Twelve months after the start of the intervention post intervention measurements will commence.

After the post-intervention measurements, the ACCOMPLISH package will be adjusted for all process evaluation information gathered and will be offered to the control hospitals. Based on experience gained from the study, they will receive instruction on how to implement the package.

## Outcome Measures

### Primary outcome measure: observed compliance rate

The compliance rate is operationalised as the number of HH practices divided by the number of opportunities for HH according to the international guidelines of the WHO [22], which state that HH must be performed before and after patient contact, after contact with patient surroundings, after body fluid exposure risk, and before aseptic tasks. Compliance will be assessed covertly by direct observation at T1(baseline), T2 (6 months post-intervention), T3 (12 months post intervention) and T4 (18 months post intervention) at the individual level by a trained observer with the electronic Dutch version of the Hand hygiene Observation Instrument [23]. All observations will be collected between 7:30 and 13:00. Each observation session will last 4-5 hours, during which time at least three different nurses will be followed in their duties. Furthermore, any physicians caring for the same patient as the nurse being followed will also be observed.

Although some HCW may be aware of the true nature of the study, most will revert to their routine quickly, reducing the Hawthorne effect [24]. In addition, the frequency of HH per ward will be collected continuously by the novel electronic dispensers. Furthermore, data on environmental factors influencing HH will be collected (such as patient to nurse ratio and the number of patients on the ward).

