### Data analysis

Process indicator questionnaires: These will be analysed with multivariable linear regression analysis, with self-reported compliance (never-always on a 10-point scale) as primary outcome variable. The determinants included in the questionnaire will include the socio-political context, the organization, the adopting person or HCW, the innovation and the facilities needed to implement the innovation [13]. Furthermore behavioural determinants will be included in the questionnaire, including attitudes, social norms, perceived behavioural control, intention, habit, knowledge of the guidelines and patient safety culture (as measured by the ComPaz questionnaire) [30].

Randomised controlled trial: The effect of the intervention strategy on the overall compliance rate among HCW (logistic regression analysis), and on prevalence of HAI will be assessed. Multilevel analysis will be performed to compensate for the clustered nature of the data (HCW are clustered within wards), using mixed linear modelling techniques.

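### Physicians, one of two target professions with their own lighter training, are sampled only through followed nurses and merged into one compliance rate, so a significant primary result need not mean that physicians improved

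*Protocol article*

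**What the plan says.** All references are to the protocol article.

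- **Who is targeted.** Under Sample for study: "Target population: nurses and physicians with direct patient contact working in the ICU or surgical ward". No headcount or share is given for either profession.
- **What they receive.** Under Intervention program: theoretical background, nurses and physicians are trained separately. Nurse teams have three interactive sessions over 3-4 months. For physicians, "The physician teams will receive one interactive group session", followed a month later by an individual web-based session. The e-learning is tailored to each profession. The Background says that different factors drive the behaviour of the two groups, and the Discussion presents the tailoring as a distinguishing feature of the trial.
- **Who is observed.** Under Primary outcome measure, each session of 4-5 hours follows nurses: "at least three different nurses will be followed in their duties". Physicians are added by a separate rule: "any physicians caring for the same patient as the nurse being followed will also be observed". Observation is made "at the individual level by a trained observer with the electronic Dutch version of the Hand hygiene Observation Instrument".
- **What is analysed.** The outcome is a single ratio: "The compliance rate is operationalised as the number of HH practices divided by the number of opportunities for HH". Data analysis states the target of inference as "The effect of the intervention strategy on the overall compliance rate among HCW (logistic regression analysis" and adds a multilevel structure in which "HCW are clustered within wards". Profession is not mentioned there.
- **How it was sized.** Sample size calculations uses one change for all staff, 20% to 50%, and 120 opportunities per ward per measurement, not divided by profession.

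**The concern.** The article describes an intervention with two professional strands and then fixes an outcome that samples one strand by design and the other by chance, and adds them together. Two consequences follow.

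First, interpretation. If physician opportunities are a modest part of the total, the overall rate is mainly a nurse rate. A significant result could then be read as support for the whole package, including the physician strand, although physicians had not changed. The Discussion looks ahead to national and international dissemination, so this reading matters.

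Second, noise. If nurses and physicians comply at different rates, the overall rate depends on the professional mix in the observed opportunities. Nothing in the observation rule holds that mix constant across wards, arms or time points, and only eight hospitals per arm are available to average it out.

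**Working it through.** **Inputs from the article:** compliance 20% rising to 50%; 120 opportunities per ward per measurement; two wards in each of eight hospitals per arm; 10% heterogeneity between wards; two-sided alpha 0.05; stated power 93%.

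**Assumptions:** the physician share of opportunities, s, is not given, so a range is used. Both professions are taken to be at 20% without intervention, because only one figure is given. The 20% to 50% change is used as the control-versus-intervention contrast. The 10% heterogeneity is read as an intracluster correlation (ICC) of 0.10.

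**1. The plan's own power**

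Effective n per arm = clusters × m / (1 + (m − 1) × ICC), followed by a two-proportion normal power formula for 20% v 50%.

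- Hospital as cluster: 8 × 240 / (1 + 239 × 0.10) = 1920 / 24.9 = 77.1; power 98.0%.
- Ward as cluster: 16 × 120 / (1 + 119 × 0.10) = 1920 / 12.9 = 148.8; power 99.99%.

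The stated 93% is not reproduced. It corresponds to an effective n of about 58 per arm, which is an ICC of about 0.14 for eight hospitals of 240 opportunities or about 0.27 for 16 wards of 120. The stated figure is lower than these readings give, and the mismatch does not bear on this point. An effective n of 58 is carried below as a cautious case.

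**2. Pooled rate when physicians do not change**

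Pooled rate = s × 20% + (1 − s) × 50%. Power is for 20% v the pooled rate.

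| s | Physician opportunities per ward (120 × s) | Pooled rate | Power, n = 77.1 | Power, n = 148.8 | Power, n = 58 |
|---|---|---|---|---|---|
| 10% | 12 | 2 + 45 = 47% | 95% | 99.9% | 88% |
| 20% | 24 | 4 + 40 = 44% | 90% | 99.5% | 80% |
| 30% | 36 | 6 + 35 = 41% | 81% | 98% | 69% |
| 50% | 60 | 10 + 25 = 35% | 55% | 83% | 44% |

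Worked example for the last column at s = 10%: the mean of 20% and 47% is 33.5%; z = (0.27 × √58 − 1.96 × √(2 × 0.335 × 0.665)) / √(0.20 × 0.80 + 0.47 × 0.53) = (2.056 − 1.308) / 0.640 = 1.17, giving 88%.

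At shares of 10% to 20%, a significant overall result is likely with no physician effect at all. The argument weakens as s rises and is much weaker at 50%.

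**3. Effect of professional mix**

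Assume nurses at 50% and physicians at 30% in both arms, so that there is no true arm difference.

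- Physician share 10%: 0.90 × 50 + 0.10 × 30 = 48%.
- Physician share 25%: 0.75 × 50 + 0.25 × 30 = 45%.

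The shift is 3 points, against a planned change of 30.

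**4. Can a physician estimate be made?**

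With the hospital as cluster, ICC 0.10 and physician opportunities only, the effective n per arm is 8 × 24 / 3.3 = 58.2 at s = 10%, 8 × 48 / 5.7 = 67.4 at 20% and 8 × 72 / 8.1 = 71.1 at 30%. A separate estimate is therefore feasible on these assumptions. They are favourable ones: they spread physician opportunities evenly and ignore the repeated opportunities of the same physician.

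**The case against.** The strongest reply is that nothing here is inconsistent. Research question 1 asks about compliance as a whole, the outcome is one ratio over all opportunities, and the analysis is of that overall rate. Pooling by opportunity also has a rationale, since patients' exposure to infection depends on contacts with all staff. This stands: the pooled test is valid for overall compliance.

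Three stronger readings are tempting and are not supported.

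- A reader might infer that physicians are half of the target population. They are one of two named professions, and no numbers are given.
- A reader might infer that the trial could meet its target without physicians. The change from 20% to 50% is a sample-size assumption; no success threshold is stated.
- A reader might infer that the mix is known to differ between arms. No data on mix are given. The same observation rule applies to both arms and hospitals are randomised, so an imbalance would be noise and not systematic bias. A gap of 15 percentage points in physician share between whole arms would be large, and even that moves the rate by only 3 points.

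Physician sampling is also less haphazard than it may look. Within a 7:30-13:00 window, every 4-hour session covers at least 9:00 to 11:30, and any physician attending the followed nurse's patient counts.

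Finally, a profession term may well be in a fuller plan that is not shown, and its absence from an article is not an error in itself. What remains is that the article does state the observation rule and the overall rate as the target of inference, alongside claims about tailoring to both professions that this rate alone cannot support.

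Reserving a fixed quota of physician opportunities is not recommended. It would impose an artificial mix and take observers away from nurses.

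**Conclusion.** The point holds as a limit on interpretation and an avoidable loss of precision. It does not invalidate the primary test. With physicians unchanged at 20% and nurses at 50%, the pooled rate would be 47%, 44% or 41% at assumed physician shares of 10%, 20% or 30%. At hospital level with an ICC of 0.10, power for significance would be about 95%, 90% or 81%; if the stated 93% is taken as the starting point, it would be about 88%, 80% or 69%. A positive primary result is therefore compatible with no physician effect when that share is modest. This rests on a share that the article does not give and on equal starting rates in the two professions; at a 50% share it is much weaker. The mix effect is secondary, about 3 points under assumed rates and shares. The change is worth making because it costs almost nothing and aligns the conclusion with the data.

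**What to change.** 1. Include profession (nurse or physician) as a fixed effect in the primary multilevel logistic model. The observation rule already distinguishes the two and observation is per individual, so it can be identified for each observed worker. State that it is to be recorded.
2. Keep the overall arm effect as the primary result. From the same model with a profession-by-arm term, report the arm effect for nurses and for physicians, each with a confidence interval and the number of opportunities behind it, by arm and time point.
3. Word the conclusion so that it covers physicians only if their own estimate supports it.

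The cost is a few lines of analysis text and one recorded item; sessions and total opportunities are unchanged. The downside is that the physician estimate will be imprecise, more so if a few physicians supply most of the opportunities, and a non-significant physician result must not be read as proof of no effect. With profession in the model, the arm odds ratio is conditional on profession, so the crude overall rates should still be shown beside it.
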